# Transfer Validity of Pediatric Supracondylar Humeral Fracture Pin Placement Practice on In-Theater Performance by Orthopedic Trainees Using an Augmented Reality Simulator: Protocol for a Pilot Interventional Cohort Study With a Retrospective Comparator Cohort

**DOI:** 10.2196/38282

**Published:** 2023-08-02

**Keywords:** pediatric orthopedics, augmented reality simulator, supracondylar humeral fractures, closed reduction and percutaneous pinning, transfer validity, fracture, surgeons, education, practice, trainees, pediatric, orthopedic, training, surgical procedure

## Abstract

**Background:**

Supracondylar humeral fractures (SCHF) are a common cause of orthopedic morbidity in pediatric populations across the world. The treatment of this fracture is likely one of the first procedures involving x-ray–guided wire insertion that trainee orthopedic surgeons will encounter in their career. Traditional surgical training methods of “see one, do one, teach one” are reliant on the presence of real-world cases and must be conducted within an operative environment. We have developed an augmented reality simulator that allows trainees to practice this procedure in a radiation-free environment at no extra risk to patients.

**Objective:**

This study aims to examine whether training on a simulator in addition to traditional surgical training improves the in-theater performance of trainees.

**Methods:**

This multicenter, interventional cohort study will involve orthopedic trainees from New Zealand in their first year of advanced training between 2019 and 2023. Advanced trainees with no simulator exposure who were in their first year in 2019-2021 will form the comparator cohort, while those in the years 2022-2023 will receive additional regular simulator training as the intervention cohort. The comparator cohort’s performance in pediatric SCHF surgery will be retrospectively audited using routinely collected operative outcomes and parameters over a 6-month period. Data on the performance of the intervention cohorts will be collected in the same way over a comparable period. The data collected for both groups will be used to determine whether additional training with an augmented reality training shows improved real-world surgical outcomes compared to traditional surgical training.

**Results:**

As of February 2022, a total of 8 retrospective comparator trainees have been recruited by email. The study is financially supported through an external grant from the Wishbone Orthopaedic Research Foundation of New Zealand (September 2021) and an internal research grant from the University of Otago (July 2021).

**Conclusions:**

This protocol has been approved by the University of Otago Health Ethics committee (reference HD21/087), and the study is due for completion in 2024. This protocol may assist other researchers conducting similar studies in the field.

**Trial Registration:**

Australian New Zealand Clinical Trials Registry ACTRN12623000816651; https://tinyurl.com/mtdkecwb

**International Registered Report Identifier (IRRID):**

DERR1-10.2196/38282

## Introduction

### Background

Supracondylar humeral fractures (SCHF) of the elbow are one of the most common orthopedic causes of morbidity in children. SCHF represent 3.3% to 16.6% of all childhood fractures, 32.6% of upper extremity fractures, and 57.5% of elbow fractures across localities [1-4]. The Gartland classification system is used for characterizing the extension type of SCHF and is dependent on the degree of humeral fragment displacement [5]. The gold standard for the management of operative cases is closed reduction and percutaneous pinning (CRPP), unless severe neurovascular compromise or an open fracture is present [6-8]. CRPP is seen as a more effective and safer method for treating displaced SCHF than nonoperative and open reduction methods [9-12].

### Current Training

The status quo of apprenticeship-style orthopedic training does not enable standardized hands-on skill practice outside of the operating room. The “see one, do one, teach one” methodology is becoming increasingly insufficient as trainees face a decrease in work hours for necessary well-being needs. This decrease in work hours means there are fewer opportunities for trainees to participate in and therefore learn from real cases. Limiting training to the operating room also incurs both financial and opportunity costs to the health care system as trainees require more time to complete procedures than consultants [13,14]. In addition to costs and reduced availability of the current method of training, there is also the question of whether apprenticeship-style teaching is really the most effective form of teaching available. Numerous studies on learning and teaching for adults have shown that independent, deliberate, and repeated practice is most effective for skill acquisition [15-18]. By nature, apprenticeship-style training allows for the repetition of individual case types but not a deliberate practice of certain aspects of the skills, such as only percutaneous pinning in CRPP.

### An Alternative Training Method

Improvements in computer technology have afforded the development of a new method of surgical training—augmented reality (AR) simulation. Using AR technology, skill acquisition can take place before entering the operating room. CRPP requires a high level of hand-eye coordination, visuospatial reasoning to interpret the X-ray image, and haptic interpretation to be able to feel the wire entering or leaving the bone. One such example was developed by our research team. The “BoneDoc AR” simulator (University of Otago) that we have produced uses an iPad app to provide real-time simulated X-ray images, while trainees are drilling through a physical model of the elbow. This physical model is made of silicone soft tissue and 3D-printed plastic bones. In addition, the simulator can provide objective measures of proficiency, such as exact pin placement, which are not possible without the use of computed tomography scans. These objective measures may be of value in providing feedback on skills acquisition during surgical training. 

### Study Overview

Appropriate validation of the BoneDoc AR simulator is necessary to determine its usefulness in surgical training. Transfer validity, the ultimate test of a surgical simulator, is the transfer of skills acquired on a simulator into the real-world operating theater. Validity tests are necessary to ensure the efficacy of a simulator in a training environment [19]. There are few surgical AR simulators, which have shown positive transfer validity, and none on AR simulators of SCHF treatment [20]. There is a clear paucity in the literature of this field, and there is a need for further research. This pilot study aims to examine the transfer validity of orthopedic trainee practice on the BoneDoc AR simulator.

We hypothesize that training with the simulator will improve in-theater performance as defined by a reduction of theater time, number of fluoroscopy images taken, postsurgical complication rates, and an increase in pinning accuracy. In all metrics, intervention trainees will be compared with retrospective-matched comparator trainees.

## Methods

### Study Setting

This multicenter, interventional cohort study will involve first-year orthopedic trainees stationed in New Zealand hospitals between 2019 and 2023.

Trainee performance will be collected across hospitals located in Invercargill, Rotorua, Timaru, Palmerston North, Whanganui, Taranaki, Tauranga, Christchurch, Waikato, and Auckland for 2022. The locations of first-year trainees in 2023 are yet to be determined. Retrospective comparator performances will be collected through training logbooks and electronic patient records.

### Eligibility Criteria

The inclusion criterion was being a full-time registered first-year orthopedic trainee in New Zealand between 2019 and 2023.

### Study Design

The intervention cohort is composed of trainees using the BoneDoc AR simulator at least once per month over a follow-up period of 6 months (May to November) in the years 2022-2023 (Figure 1).

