### Interventions and Comparators

#### Intervention

The simulator will be first administered at the March training weekends for each year. We will use these training weekends to test participants at baseline on the simulator and collect demographic data via survey. The simulator will be set up as one of the 15-minute assessment stations in the training weekend. Simulator sets will be distributed to individual trainees following the training weekend. Upon delivery of the simulator sets, the principal investigator will also provide aid to the trainee in identifying an appropriate environment for the simulator and address any setup issues.

It is then expected that trainees will undertake, at minimum, monthly 15-minute practices on the simulator for the next 6 months of training. These practice data are sent to a cloud server after each use. Note that the simulator training will be in addition to any routine training they will receive at their respective hospitals. Over this time, primary end points for each in-theater case will be taken over the course of follow-up through District Health Board (DHB) records, including patient picture archiving and communication system (PACS) records and trainees’ logbooks.

We will request intervention trainees to write out relevant patient data and end point results as the cases present to maximize accuracy. Trainees will be reminded monthly by email to provide case data and practice on the simulator. Their simulator performance will be assessed again in a controlled environment during the November training weekend. At this point, secondary end points will also be collected via survey.

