### Statistical Analysis

Operative outcomes using data taken before or without ongoing exposure to the simulator will be compared to outcomes using data from trainees who have used the simulator after 1 year. Comparisons will be performed using Student *t* tests or Wilcoxon Rank Sum tests (depending on the distribution of the data) for theater time and chi-square or Fischer exact tests (depending on the count of the outcome) for the number of complications, number of accurate pin placements, and number of mistakes.

Primary end points will be plotted on separate cumulative sum curves to show trends in performance over the course of follow-up by individuals and aggregated according to pre- and post–1-year simulator training. Control limits will be determined based on values identified in the literature and consultation with senior orthopedic consultants [22-24].

Accuracy of pin placements in subsets of images measured twice must be based on anterior-posterior, lateral, and oblique radiographs. Measurements taken will need to be compared for intra- and interobserver reliability using Bland-Altman plots and intraclass correlation scores.

The results from the familiarity questionnaire will be summarized as responses per category.

Univariable ordinary least squares regression analyses will be used to examine the association of theater time, number of complications (including nonideal unions), and number of x-ray shoots with independent variables. Logistic regression will be used to examine the association of accurate pin placement (yes or no) with independent variables. Independent variables will be the number of times the simulator is used, the number of SCHF procedures performed prior to intervention, Gartland classification, scores on tests of spatial awareness, and the number of SCHF procedures performed during the intervention. Independent variables that are significantly associated with a primary end point (*P*<.05) will be included as covariates in multivariable analyses. Appropriate model diagnostics, and where required, data transformations will be used.

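### The intervention cohort is defined by actual monthly simulator use in one place and by training year and enrolment elsewhere; the use-based definition would select on adherence and should be reworded

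*Protocol article*

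**What the plan says.** The protocol article describes membership of the intervention cohort in two ways.

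**By use.** Study Design consists of one sentence: "The intervention cohort is composed of trainees using the BoneDoc AR simulator at least once per month", with the six-month follow-up, the months and the years added. Statistical Analysis also sorts data by use. The reference side is "Operative outcomes using data taken before or without ongoing exposure to the simulator", and the other side is data from people who made use of it.

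**By year, status and enrolment.**
- The Abstract (Methods) says that "those in the years 2022-2023 will receive additional regular simulator training as the intervention cohort", and defines comparators as unexposed first-year trainees of 2019-2021.
- Eligibility Criteria has a single condition and no usage requirement: "The inclusion criterion was being a full-time registered first-year orthopedic trainee in New Zealand between 2019 and 2023".
- Recruitment enrols intervention trainees at the March training weekends, before any use during follow-up can be known.
- Intervention treats monthly practice as a regimen: "It is then expected that trainees will undertake, at minimum, monthly 15-minute practices on the simulator for the next 6 months of training". It is supported by prompts: "Trainees will be reminded monthly by email to provide case data and practice on the simulator".

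The number and frequency of simulator uses are secondary end points, and the number of uses is an independent variable in the regressions.

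**The concern.** Whether a trainee practised every month is known only at the end of follow-up. A cohort defined that way is selected on behaviour after enrolment. The 2019-2021 comparators face no equivalent test of diligence. If trainees who keep practising would have operated better anyway, part of any observed difference reflects who kept practising. The stated objective is the effect of adding the simulator to traditional training, and that needs a cohort fixed when the simulator is handed out.

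Matching on length of training and collecting baseline variables, which the Discussion relies on, does not correct selection on later behaviour. A use-based rule would also cut off the low end of the use measures that the study wants to report and to regress on. Cohort membership feeds every primary comparison, so an unresolved conflict could be settled after outcomes have been seen.

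**Working it through.** **1. The plan's own head count.** Recruitment gives 41 comparators, an average of 12 new trainees a year, two intervention years, and a total of about 65.
- 41 + 2 × 12 = 65, which reproduces the stated total.
- With the 14 trainees planned for 2022 and 12 for 2023: 41 + 14 + 12 = 67, also consistent with an approximate 65.

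The total therefore counts every expected 2022-2023 trainee. It agrees with the Study Design definition only if adherence is complete.

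**2. How demanding the use-based rule is.** Assume independent monthly compliance *c*. The share using the simulator in all six months is *c*⁶.
- *c* = 0.95: 0.735, about 18 of 24.
- *c* = 0.90: 0.531, about 13 of 24.
- *c* = 0.80: 0.262, about 6 of 24.

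**3. Spurious shift if low users are dropped and there is no true effect.** Let *k* be the share retained (the most adherent) and ρ the correlation between adherence and performance. The protocol gives neither, so both are assumptions. With adherence taken as normal,

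shift in SD = ρ × φ(z₁₋ₖ) / *k*.

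The last column gives the rejection rate of a nominal two-sided 5% z-test with 41 comparators against 24 × *k* intervention trainees.

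| Retained *k* | Intervention n | Shift, ρ = 0.2 | ρ = 0.3 | ρ = 0.5 | Rejection rate, ρ = 0.2 to 0.5 |
|---|---|---|---|---|---|
| 0.90 | 22 | 0.039 | 0.058 | 0.097 | 5% to 7% |
| 0.75 | 18 | 0.085 | 0.127 | 0.212 | 6% to 12% |
| 0.50 | 12 | 0.160 | 0.239 | 0.399 | 8% to 23% |

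Example: for *k* = 0.50, φ(0) = 0.399 and 0.399 / 0.50 = 0.798; multiplied by 0.5 this is 0.399 SD. With ρ = 0 the shift is zero and the rejection rate stays at 5%, but the cohort still shrinks.

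**4. Selection on the comparator side.** Comparators are approached by email for consent. The Results section reports 8 recruited as of February 2022, and 8/41 = 19.5%. If response depended on engagement with the same ρ of 0.2 to 0.5, the same formula at *k* = 8/41 moves the comparator mean by 0.28 to 0.71 SD in the opposite direction. Recruitment dates the start of comparator enrolment to that same month, so 8 of 41 is an early count and not a final response rate. The calculation shows only that the two selections can oppose each other.

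**5. After the fix.** If all enrolled 2022-2023 trainees are kept, the intervention cohort stays at about 24, the total at about 65, and the shift from filtering on use is zero.

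**The case against.** The strongest reply is that the Study Design sentence describes the intended regimen and is not an exclusion rule. No section removes a low user. The single eligibility criterion, March enrolment, the head count and the reminders all point to a cohort fixed at enrolment. Measuring use as an end point and a regressor presupposes that it varies among retained trainees. This stands, and it rules out saying that less engaged trainees do leave the cohort. It does not remove the conflict: no section says that low users are kept, and two sections define the groups by use.

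A reader might also infer three stronger points that the document does not support.
- *Lapsed trainees would be counted as reference.* The Statistical Analysis wording is loose enough to suggest it. But the Abstract and Recruitment confine comparators to unexposed trainees of 2019-2021, and every intervention trainee is tested on the simulator at the March weekend.
- *Comparators are unfiltered.* They face no practice condition, but they are self-selected by email consent.
- *The result is therefore biased towards the simulator.* Comparator selection may act the other way, so the net direction is not established. Nor can opposing biases be assumed to cancel.

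It can also be said that handling of non-adherence belongs in a statistical analysis plan. That would answer a silence. Here the article states a definition that disagrees with its other sections.

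**Conclusion.** The concern holds as an internal contradiction about who belongs to the intervention cohort. One of the two readings would introduce selection on adherence after enrolment. Under that reading the spurious shift is about 0.04 to 0.40 SD towards the simulator for assumed retention of 90% to 50% and an assumed correlation of 0.2 to 0.5, and nil if adherence is unrelated to performance. The expected intervention cohort of about 24 would fall to between 22 and 12 over the same retention range. These sizes are conditional on low users actually being dropped, which the protocol does not say. They describe one selection process and not the net bias of the study, whose direction is open. The point should be settled before analysis because it governs every primary comparison, but it needs only a clarification of wording.

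**What to change.** - Reword Study Design so that the intervention cohort is all enrolled 2022-2023 first-year trainees given a simulator set, analysed in that cohort whatever their use.
- Keep monthly practice as the expected schedule, as the Intervention section already has it.
- Reword Statistical Analysis to compare this cohort with a reference group made up only of the 2019-2021 trainees, so that no 2022-2023 trainee can be counted as reference.
- Report the subset who practised at least monthly as a labelled sensitivity analysis.

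The cost is wording only: no extra data and no loss of sample. Low users may dilute the estimate slightly, but the result then answers the stated question of what adding the simulator to training achieves.

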**Figure 1 figure1:**
[figure not shown]
Schematic representation of the intervention and comparator data collection timeline.

### Recruitment

Intervention group trainees will be approached at training weekends to inform them about the study, to assess eligibility, and to receive consent. Comparator group trainees will be identified from the New Zealand Orthopaedic Association trainee registry and approached via email for this process. Enrollment for comparator group trainees will begin in February 2022, and enrollment for intervention group trainees will occur in the March training weekends of 2022 and 2023.

We aim to include data for 14 trainees in 2022; however, the number of trainees in 2023 is not yet known. The comparator cohort data will be retrospectively audited from trainees who undertook traditional training without exposure to the simulator during their 6 months of follow-up in the years 2019, 2020, and 2021 (n=41). We expect a total sample size of approximately 65 trainees, given an average of 12 new trainees per annum. The comparator group is matched based on their length of registered training at the start of follow-up, that is, first-year trainees with 2 months of registered training.

The in-theater performances of the comparator and intervention groups will be compared using cumulative sum charts for each of the primary outcomes to determine any differences in trends of skill acquisition according to the method of training. The simulator performance of the intervention group will be used to establish a learning curve and compared with in-theater learning curves.

Retrospectively matched trainees have been chosen instead of prospective randomized ones for the comparison group in order to maximize sample size and to avoid contamination. New Zealand only introduces 10-15 trainees per year into the orthopedic training program, and thus a prospective randomized trial will greatly limit the statistical power. There is also the chance of cross-group contamination as there is no way of ensuring comparator trainees located in the same area as intervention trainees will not use the simulator.

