### Conclusions

The results of this pilot study will show the feasibility and efficacy of simulator use within New Zealand’s public health system. The long-term benefits to society will be both for the education of registrars and the health outcomes of patients. In particular, for trainees in localities with lower populations, this simulator can address the disparity in case volumes for those that would otherwise have been deprivileged by their location. Moreover, this simulator has been developed with minimizing costs and increasing accessibility as key objectives; it is cheaper than many currently available models and has low requirements for the environment. We envisage its frequent use as a valuable tool within hospital systems.

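### Hospital is neither a matching factor nor a listed covariate and the comparator hospitals are not stated, so site differences may be mixed with the simulator effect

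*Protocol article*

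**What the plan says.** All references are to the protocol article.

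- **Matching (Recruitment).** "The comparator group is matched based on their length of registered training at the start of follow-up". Strengths and Limitations again gives training experience as the matching basis. No other factor is named.
- **Sites (Study Setting).** The study covers "first-year orthopedic trainees stationed in New Zealand hospitals between 2019 and 2023". Intervention sites are "Invercargill, Rotorua, Timaru, Palmerston North, Whanganui, Taranaki, Tauranga, Christchurch, Waikato, and Auckland for 2022", and "The locations of first-year trainees in 2023 are yet to be determined". No list is given for the 2019-2021 comparators, and no overlap of hospitals is required.
- **Case data (Patient Data).** The listed items cover patient and fracture details and whether a consultant or other assistant was present. Hospital is not among them.
- **Analysis (Statistical Analysis).** The cohorts are compared by t or rank sum tests and by chi-square or exact tests, without adjustment. The regressions use simulator uses, earlier procedures, Gartland class, spatial awareness scores and procedures during the intervention. A variable enters the multivariable model only if its univariable P value is below .05.
- **Mitigation (Strengths and Limitations).** Confounding from historical comparators is admitted. Unnamed potential confounders will be collected and explored, and a difference-in-difference analysis is planned.

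**The concern.** Simulator practice is added to whatever routine training the trainee's own hospital provides (Intervention), so the background condition is specific to the site. Theater time and fluoroscopy counts may plausibly depend on local theater and imaging practice as well as on trainee skill. If the mix of hospitals differs between the cohorts, the outcomes can differ with no simulator effect at all, in either direction. Matching on months of training does not address this, nor do Gartland class or trainee experience.

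This goes beyond a detail that an article leaves to a fuller document. The article itself states the matching factor and names the regression variables, and hospital is in neither.

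**Working it through.** **1. Sample size.** The plan expects about 65 trainees: 41 comparators + 2 intervention years × 12 = 65, so the intervention cohort is 65 − 41 = 24. The only firmer intervention figure is "We aim to include data for 14 trainees in 2022; however, the number of trainees in 2023 is not yet known"; using 14 + 12 gives 67, which is also close to the stated total. Over ten sites, 24 trainees is 24/10 = 2.4 per site.

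**2. Where hospital could enter.**

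| Step of the plan | Hospital included? |
|---|---|
| Matching | No, length of training only |
| Listed case data | No |
| Between-cohort tests | No, unadjusted |
| Listed regression variables | No |
| Cumulative sum limits | No, from literature and consultants |
| Confounders to be explored | Not named |
| Difference-in-difference | Not named |

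**3. Does the difference-in-difference analysis remove it?** A constant site difference in level cancels only against a reference period at the same site that the simulator has not affected. The simulator is first used in March (Intervention), and intervention follow-up runs from May to November (Study Design). No in-theater period before exposure is defined. A contrast of early with late follow-up would cancel a constant site offset, but also any simulator benefit already present when follow-up starts.

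**4. Possible size (illustration).** The documents give neither hospital overlap nor between-hospital variance. Assumptions: one summary value per trainee with total SD 1; a share ρ of the variance due to hospital; each cohort spread evenly over ten hospitals; k hospitals common to both; hospital effects stable over the years.

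- Variance used by the unadjusted test: 1/41 + 1/24 = 0.0661, SE = 0.257.
- Sum over hospitals of squared differences in cohort shares: S = 2(10 − k) × 0.1².
- SD of the hospital offset: √(ρS).
- True variance: (1 − ρ) × 0.0661 + ρS.
- True two-sided error rate: 2[1 − Φ(1.96 × 0.257 / true SE)].

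| Shared hospitals k | S | ρ | Offset SD | True SE | True error rate |
|---|---|---|---|---|---|
| 10 | 0 | 0.05 | 0 | 0.251 | 4.4% |
| 10 | 0 | 0.30 | 0 | 0.215 | 1.9% |
| 5 | 0.10 | 0.05 | 0.07 | 0.260 | 5.3% |
| 5 | 0.10 | 0.30 | 0.17 | 0.276 | 6.8% |
| 0 | 0.20 | 0.05 | 0.10 | 0.270 | 6.2% |
| 0 | 0.20 | 0.30 | 0.24 | 0.326 | 12.2% |

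Example for k = 0, ρ = 0.30: 0.70 × 0.0661 + 0.30 × 0.20 = 0.1062, SE = 0.326; 1.96 × 0.257/0.326 = 1.545, which gives 12.2%.

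With identical hospitals and shares there is no offset, and the unadjusted test is conservative. The answer turns on overlap, which the article does not report.

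**The case against.** The strongest reply is that nothing shows the cohorts worked in different hospitals. Both come from one national first-year program, and the article describes the study as spanning all New Zealand centers, so substantial overlap fits the text at least as well as its absence. This stands. A reader might infer from the open 2023 sites and the unlisted comparator sites that the cohorts did rotate through different hospitals. The document does not say so; the mixing is a risk and not an established fact.

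A reader might also take the closing remark that "for trainees in localities with lower populations, this simulator can address the disparity in case volumes" as an admission that theater time or imaging differs by site. It concerns case volume only, and procedure counts before and during the intervention are already listed as independent variables. No passage documents local differences in theater time or fluoroscopy; that part rests on plausibility.

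Nor is the plan without safeguards. It admits confounding, promises to explore confounders, plans a difference-in-difference analysis and records consultant or assistant presence. These count, but the first names no variable, the second has no defined reference period, and consultant presence is not among the regression variables.

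Finally, this is a pilot with few trainees per site. That is a good argument against matching on hospital, hospital strata or hospital-specific cumulative sum baselines. It is not an argument against recording hospital and modeling it, since the article states an efficacy hypothesis and expects its results to show efficacy.

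**Conclusion.** The point holds as a gap in the stated design and analysis. Followed as written, the plan leaves any site difference in theater time and fluoroscopy use inside the unadjusted cohort contrast, and the general mitigations do not clearly take it out.

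The size cannot be determined from the document. Under the assumptions above, the inflation is small with half the hospitals shared (5.3% to 6.8%) and reaches 12.2% only with no shared hospital and 30% of the variance due to hospital. With the same hospitals in the same shares there is no inflation. No estimate in minutes or in fluoroscopy shots can be supported. The change is worth making because it is cheap and because the present plan would not show which of these cases applies.

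**What to change.** 1. Add the treating hospital to the case data, taken from the District Health Board record that each case already draws on.
2. Report the number of trainees and cases by hospital and cohort, so that the overlap is visible.
3. Fit the between-cohort models with a cohort term and random intercepts for hospital and trainee. Include these regardless of the univariable P value, outside the P<.05 selection rule.
4. Add a sensitivity analysis restricted to hospitals that contribute cases to both cohorts.
5. State the reference period of the difference-in-difference analysis, or say that it compares trends within follow-up only.

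The cost is one data field and some analysis wording; recruitment and the intervention do not change. Some precision is lost, and more if overlap is poor. A random intercept pools partly across sites, so it does not give a purely within-hospital contrast; the shared-hospital analysis is there to check what remains. With about 2.4 simulator trainees per site, hospital matching, hospital strata and hospital-specific cumulative sum baselines are not proposed.
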